### Statistical analysis

Statistical analysis will be undertaken using both intention-to-treat (ITT) and per-protocol (PP) analyses. For the ITT analysis, all patients who undergo the Zelen-type randomization and received at least one treatment will be analyzed. Primary PP data analysis will also be undertaken for all patients who have high compliance (patient compliance rates equal to or greater than 80%) and do not use drugs or treatments prohibited by the protocol during treatment.

The statistical analysis will take the form of a non-inferiority test. The margin of non-inferiority is -2. For the main outcome, we will calculate the 95% confidence interval for the difference in NRS pain score between the treatment group and the control group. If the lower limit is greater than -2, non-inferiority will be considered valid.

For continuous data, mean ± standard deviation will be used to describe data that conforms to a normal distribution, whereas non-normally distributed continuous data will be described as the median (interquartile spacing). Where the data conforms to a normal distribution, independent sample t-test will be used for comparison between the two groups with homogeneity of variance; otherwise, a t-test will be used with heterogeneity of variance. Wilcoxon rank-sum test will be used if data does not conform to a normal distribution. Categorical data will be represented by frequency or percentage and compared using chi-square test or Fisher exact test. Missing data will be replaced according to the last observation carried forward method. The 95% confidence interval will be calculated, and *P* < 0.05 will be considered to indicate a significant difference. All statistical analysis will be performed using SPSS software (version 20.0).

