Traditional moxibustion (TM) is a commonly used alternative therapy for KOA in Asia [11, 12]. The efficacy of TM is considered to result from a combination of factors [13–15], among them, near-infrared (NIR) light is generally thought to play a major role in the biological radiation effect of moxibustion. The NIR radiation can induce active substances to promote the metabolism and thermogenesis of the organs reached by the NIR rays, thereby adjusting the body’s immune and neurological functions by energizing cell metabolism [16–18]. Other studies indicated that photobiomodulation plays an active role in anti-inflammatory and analgesia [19, 20]. In recent years, the Chinese regime has been greatly emphasizing on the integration of traditional Chinese medicine (TCM) instruments with modern science and technology, and some novel moxibustion instruments have been developed to minimize the adverse effects of TM while maintaining its effectiveness [21–24]. However, the currently available instruments have two major problems: (1) the working temperature is much lower than the burning temperature of natural moxa pillars; and (2) the characteristics of moxibustion burning infrared spectrum have not yet compiled a unified standard, so none of these instruments can actualize a high simulation of the natural moxibustion emission spectrum and hindering the therapeutic effects.

For the above reasons, we will set up an infrared emissivity test system to accurately test for a reliable basic data of moxibustion emission spectrum, and then regulate the emission spectrum of the material by regulating the composition structure of infrared ceramics/graphene to realize the coupling between it and the absorption spectrum of human acupoints [25]. On this basis, we use a Mg–ZrO2/ graphene specified composite ceramic block as the key material of emission light source to develop infrared laser moxibustion (ILM). Therefore, we designed a Zelen-design randomized controlled non-inferiority clinical trial to (1) preliminarily investigate whether ILM is non-inferior to TM in reducing pain and improving function in patients with KOA; and (2) provide clinical evidence to verify whether ILM can become a safe and reliable clinical alternative to TM in the future.

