### Interventions

Moxibustion treatment in the two groups (approximately 30 min in duration) will be administered three times per week over six weeks, and a follow-up evaluation will be performed at week 10. During the trial period, the participants will be prohibited from receiving relevant treatments, such as knee surgery, diagnostic arthroscopy, intra-articular injection, physiotherapy, acupuncture, massage therapy, and acupoint application.

Both knees of subjects with bilateral osteoarthritis will be treated, but only the most painful knee will be selected for evaluation in each subject. If both knees are equally painful, the knee with the higher KL grade will be chosen [35], if the knee pain and KL ratings are the same on both sides, the knee joints for evaluation will be randomly selected using a random number table.

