### Combined medication

The use of hormones and opioids will be prohibited during the trial. Participants who have taken medication for hypertension, diabetes, or knee pain in the month prior to the start of the trial will continue to take medication during the study but will be required to specify the medication in the case report form (reasons, drug name, type, dose, the time of the intake, and whether the symptoms are relieved after taking the medicine). If the participants are not taking any medications before the trial, they will not take any medications during the study. If the patient develops new symptoms or diseases during the trial, any new drug should be approved by the investigator and should only be used if it does not affect the results of trial.

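### The plan calls the per-protocol analysis primary and gives one non-inferiority criterion for two analysis sets, without saying which set decides or that both must pass

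*Protocol article*

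**What the plan says.** The Introduction sets the aim: to "preliminarily investigate whether ILM is non-inferior to TM in reducing pain and improving function in patients with KOA". Under Statistical analysis, "Statistical analysis will be undertaken using both intention-to-treat (ITT) and per-protocol (PP) analyses". The ITT set is defined first: "all patients who undergo the Zelen-type randomization and received at least one treatment will be analyzed". Then comes "Primary PP data analysis will also be undertaken for all patients who have high compliance", compliance being specified as "patient compliance rates equal to or greater than 80%) and do not use drugs or treatments prohibited by the protocol during treatment". The same section gives one decision rule: non-inferiority holds if the lower limit of the 95% interval for the NRS difference is above -2. The rule names no analysis set.

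Two other sections settle what counts as prohibited. Interventions bars treatments "such as knee surgery, diagnostic arthroscopy, intra-articular injection, physiotherapy, acupuncture, massage therapy, and acupoint application". Combined medication bars hormones and opioids and separates two groups. For those on no medication at entry, "If the participants are not taking any medications before the trial, they will not take any medications during the study" (a new drug for new symptoms needs the investigator's approval). Those already taking medication, including for knee pain, "will continue to take medication during the study but will be required to specify the medication in the case report form".

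**The concern.** Two analyses and one criterion leave three possible rules: ITT decides, PP decides, or both must pass. The text chooses none of them, and the only set it labels primary is PP. A team following the text could rest the claim on PP alone, or on whichever set passes.

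This matters because of how PP is formed. A participant whose knee still hurts may seek an injection, physiotherapy, acupuncture or massage, or may stop complying. Each of these removes the participant from PP, after randomisation and possibly because of the outcome. If ILM is truly worse and such exclusions are commoner there, PP loses more poor responders from the ILM arm and the observed deficit shrinks. In a non-inferiority trial that error favours the new device.

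**Working it through.** **The plan's own figure.** The printed SD of 26.63 is on a 0-100 scale; divided by 10 it is 2.663. With margin 2, true difference 0, one-sided alpha 0.025 and 80% power, n per arm = 2 × 2.663² × (1.960 + 0.842)² / 2² = 27.8, so 28, or 29 by the exact t calculation. That matches the stated 29. The stated 37 is 29 × 1.25 = 36.25, rounded up.

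**Inputs from the plan.** Margin 2 NRS points; 37 per arm; SDs 26.63 (experimental) and 15.07 (control), here 2.66 and 1.51; 25% maximum dropout.

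**Assumptions.** The share leaving PP is 25%, borrowing the dropout figure because the plan gives no PP exclusion rate. The chance of leaving PP is logistic in week-6 NRS, with slope 0 (unrelated to pain), 0.25 (odds up about 28% per point, e^0.25 = 1.28) or 0.5 (odds up about 65% per point, e^0.5 = 1.65). Outcomes are normal. LOCF and Zelen switching are not modelled.

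**Check.** ILM is set truly 2 points worse (means 6 and 4), so every non-inferiority result is false and the nominal rate is 2.5%. There are 20,000 trials per setting with a Welch 95% CI. The CI is judged in the direction in which more pain on ILM counts against ILM.

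False non-inferiority on PP alone:

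| SDs (ILM / TM) | slope 0 | slope 0.25 | slope 0.5 |
|---|---|---|---|
| 2.66 / 1.51 | 2.4% | 9.2% | 25.9% |
| 2.16 / 2.16 | about 2.5% | 3.6% | 7.2% |
| 1.5 / 1.5 | about 2.5% | 3.0% | 5.9% |

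- With SDs 2.66 / 1.51, exclusions are 30% (ILM) and 20% (TM) at slope 0.25, and the mean PP difference is 1.62 instead of 2.00. At slope 0.5 they are 34% and 16%, with a difference of 1.25.
- With a common SD the bias is only about 2-14% of the margin. Repeat runs moved the figures by at most about one percentage point, hence the rounded ranges 3-7% and 9-27%.
- ITT, if the prohibited treatment changes nothing: 2.3-2.8%.
- Claim if either set passes: 3.5-4.3% even at slope 0.
- Claim only if both pass, no relief from other treatment: 1.2-2.4%.
- If those leaving PP also gain 2 points of relief (a further assumption), SDs 2.66 / 1.51: ITT 5.8% and 12.1% at slopes 0.25 and 0.5; both sets 4.0% and 10.4%.

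**A different exclusion model.** Suppose participants below the 10th or 20th percentile of TM response leave PP with probability q, with SD 2.164 or 2.663 in both arms. PP error is about 4% at q = 0.25, 6.5-9% at 0.5 and 14-19% at 0.75. The direction is the same.

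**Power if both sets must pass, true difference 0.** It is about 90% or more at the three SD pairs in the table. At SD 2.663 in both arms, the value that reproduces the plan's 29, PP sets the ceiling. With 37 × 0.75 = 27.75 per arm, 2 / (2.663 × √(2/27.75)) - 1.960 = 0.84, which is about 80%, the plan's own target. For ITT with 37 the same formula gives 1.27, about 90%.

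**The case against.** Running ITT and PP side by side is normal in a non-inferiority trial, and the plan does so. ITT is defined first, PP is something that will also be done, and no sentence lets PP decide alone. 'Primary' may be loose wording, or may refer to the primary outcome. This stands as far as it goes: a reader might infer that the plan discards treatment failures and decides on what remains, and the text does not support that. The ITT set keeps them.

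Three more limits stand. Compliance is not defined, so reading 80% as at least 15 of 18 sessions (0.80 × 18 = 14.4) is an inference. Continuing knee-pain medication taken before entry is allowed and is not an exclusion, so not all analgesic use leads out of PP. The exclusion rate and its link to pain are assumed. With no link PP is unbiased, and if TM lost more participants to adverse events the bias could run against ILM.

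A reader might also infer that ITT is equally compromised. That requires the other treatment to relieve pain materially in those who used it, which the documents neither state nor quantify. Without such relief ITT holds its nominal rate.

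An unseen analysis plan might settle the deciding set. But this article itself states the criterion and attaches the label. Its Discussion also concedes that poor adherence may lead to wrongly rejecting the null hypothesis, and the remedy it gives is the Zelen design. That design addresses willingness at allocation, not other treatment during the six weeks.

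**Conclusion.** The point holds as a badly fixed decision rule. The plan has two analysis sets, one criterion and no deciding set, and the primary label sits on the set that is open to outcome-related exclusion. The cost does not depend wholly on assumed pain-related exclusion: with exclusion unrelated to pain and 25% excluded, a claim on either set already carries about 3.5-4.3% error against 2.5%. If exclusion rises with pain, PP alone carries about 3-7% with a common SD and 9-27% with SDs of 2.66 and 1.51. The upper range rests on giving ILM the larger SD as well as on the stronger pain link, so it shows what could happen and is not a forecast. The documents do not show that the bias will occur, nor that PP alone will decide.

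**What to change.** In Statistical analysis:

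1. Delete 'Primary' before the PP analysis.
2. State that non-inferiority is claimed only if the 95% CI meets the margin in both the ITT and the PP set.
3. Report the number of PP exclusions and their reasons by arm.

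This costs a few sentences. Medication use and reasons for missing data already go into the case report form. The claim becomes slightly stricter, with a little less power when ILM is truly equivalent: still about 90% or more at the tabulated SDs, and at most about 80% at SD 2.663 in both arms. Requiring both sets does not remove all bias if other treatment relieves pain, which is why the exclusions by arm should stand beside the result.

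An analysis that scores those leaving PP as zero change at the same margin should not be added as a safeguard. It pulls the arms together. With 25% of each arm set to zero change, unrelated to pain, and equal baseline means, a true difference of 2 becomes 0.75 × 2 = 1.50. In simulation a truly 2-point-worse ILM then passes in 14-34% of trials across the settings examined, including those where PP is unbiased.

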#### Primary outcome

The primary outcome, to be assessed at the end of the last treatment at week 6, is the change in pain from baseline using the NRS index [38]. The NRS index typically uses a 0–10 range instead of words to represent the degree of pain experienced by the subject: 0 indicates no pain; 1–3 indicates mild pain (occasional pain that generally does not interfere with walking); 4–6 indicates moderate pain (frequent pain that interferes with walking); 7–9 indicates severe pain (sustained pain that seriously interferes with or prevents walking); and 10 indicates the worst/overwhelming pain. At the time of the evaluation, participants will be asked to mark the number on the scale that best represents their pain level in the last 24 h.

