### Sample size calculation

This study is a randomized controlled non-inferior trial. Based on the literature, the smallest clinically significant difference in the pain NRS is 2 points [44–46]. Thus, we set the non-inferiority margin to − 2. The NRS score of the subjects after treatment was taken as the main outcome index. According to the results of similar studies, [47] the average NRS score of the experimental group was 40.53 ± 26.63, and that of the control group was 41.58 ± 15.07. So we used PASS 15 to calculate the sample size (29 participants in each group), *α* = 0.025, 1 − *β* = 80%. Considering that a maximum of 25% dropped out during the trial, we ultimately plan to recruit 74 participants (37 in each group) to ensure the target sample size is obtained. The calculation results of sample size are provided as Additional file 2.

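### The non-inferiority rule is reversed as written: on a pain score where higher is worse, a lower limit above -2 puts no bound on how much worse ILM may be

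*Protocol article*

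**What the plan says.** All references are to the Methods of the protocol article.

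- **Scale (Primary outcome).** At the low end, "0 indicates no pain"; at the high end, "10 indicates the worst/overwhelming pain". A higher score is a worse result.
- **Arms (Randomization and informed consent).** ILM is the treatment group and TM the control group.
- **Endpoint (Primary outcome).** The week 6 endpoint "is the change in pain from baseline using the NRS index". The sign of the change is not given.
- **Endpoint (Sample size calculation).** "The NRS score of the subjects after treatment was taken as the main outcome index". This is a raw post-treatment score, and the margin of -2 is set in the same paragraph.
- **Contrast and rule (Statistical analysis).** "The margin of non-inferiority is -2", then "we will calculate the 95% confidence interval for the difference in NRS pain score between the treatment group and the control group", and finally "If the lower limit is greater than -2, non-inferiority will be considered valid".

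**The concern.** A lower-limit rule with a negative margin suits an outcome on which larger values are better. Here larger values mean more pain. With ILM minus TM on the pain score, inferiority of ILM lies on the positive side, and it is excluded only when the upper confidence limit lies below +2. The rule as written looks at the other side.

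This is the article's only criterion for its primary claim. Its conclusions would use a positive result to support ILM as an alternative to TM. An analyst who followed the text literally could report non-inferiority for a device that is worse by the plan's own 2-point threshold, or deny it to a device that is better. If the sign stays open, it can also be settled after the data have been seen.

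**Working it through.** **1. Direction.** Let D = mean NRS for ILM minus mean NRS for TM.

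| Outcome and contrast | ILM worse gives | Rule that excludes inferiority | Does the written rule do this? |
|---|---|---|---|
| Post-treatment score, ILM − TM | D > 0 | upper limit < +2 | No |
| Change as week 6 − baseline, ILM − TM | D > 0 | upper limit < +2 | No |
| Reduction as baseline − week 6, ILM − TM | D < 0 | lower limit > −2 | Yes |
| Score or week 6 − baseline change, TM − ILM | D < 0 | lower limit > −2 | Yes |

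The first row matches the wording of the Sample size and Statistical analysis sections. The article states neither of the conventions in the last two rows.

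**2. Inputs for the size of the effect.** The Sample size section gives SDs of 26.63 (experimental) and 15.07 (control), 29 evaluable patients per arm, α = 0.025 and 80% power. Means of about 40 cannot come from a 0–10 scale, so I assume a 0–100 scale and divide by 10, giving SDs of 2.663 and 1.507.

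**3. The plan's own figure.** With both SDs, a t-test calculation at 80% power gives 18 to 22 per arm, depending on whether the distance from the true difference to the margin is 2.105, 2.0 or 1.895. It does not give 29. With SD 2.663 in both arms and a true difference of 0, it gives exactly 29 (power 0.80). I use that setting first and then the two-SD setting. The direction problem does not depend on which is right.

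**4. Written rule, SD 2.663 in both arms, 29 per arm.**

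- SE = 2.663 × √(2/29) = 0.699, with df = 56 and t(0.975) = 2.003.
- CI half-width = 2.003 × 0.699 = 1.40.
- The rule passes when observed D exceeds −2 + 1.40 = −0.60. That includes every result in which ILM does worse than TM. It fails ILM once ILM is observed to be better by more than about 0.60 points.
- The probability of passing comes from the non-central t distribution with non-centrality (D + 2)/0.699. At D = +2 this is 4/0.699 = 5.72, giving 0.9999. At D = −2 it is 0, giving 0.025.

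**5. Written rule, SDs 2.663 and 1.507, 29 per arm (Welch interval).**

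- SE = √((2.663² + 1.507²)/29) = 0.568, with df about 44.3.
- Half-width = 1.14, so the cut is at observed D = −0.86.

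**6. Probability of declaring non-inferiority, 29 per arm.**

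| True D (ILM − TM) | Written rule, SD 2.663 both | Written rule, SDs 2.663/1.507 | Upper limit < +2, SD 2.663 both | Upper limit < +2, SDs 2.663/1.507 |
|---|---|---|---|---|
| +3 (ILM worse) | 1.000 | 1.000 | 0.0004 | 0.0001 |
| +2 | 0.9999 | 1.000 | 0.025 | 0.025 |
| +1 | 0.988 | 0.999 | 0.29 | 0.41 |
| 0 | 0.80 | 0.93 | 0.80 | 0.93 |
| −1 | 0.29 | 0.41 | 0.988 | 0.999 |
| −2 (ILM better) | 0.025 | 0.025 | 0.9999 | 1.000 |

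The two rules mirror each other and agree only at D = 0. With 37 per arm and the two-SD setting, the half-width is 1.01, the cut moves to −0.99, and the pass rates are still about 1.000 at +2 and 0.025 at −2.

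**The case against.** The strongest reply is that the sign is undefined rather than shown to be wrong. The article gives no formula and no explicit order of subtraction; ILM minus TM is inferred from the order in which the groups are named. The primary outcome is a change from baseline without a stated sign, and the Introduction speaks of reducing pain. If change were scored as benefit, a negative margin with a lower-limit rule would be the standard form. TM minus ILM would rescue the rule equally well. The PASS output in Additional file 2 is not shown and might reveal the direction that was entered. The pass rates also rest on a rescaling and, in one setting, on an equal-SD assumption, neither of which is in the article.

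Part of this stands. The investigators may well have intended one of the conventions that make the rule correct, and the figures apply only to ILM minus TM. But no section states such a convention. The section that sets the margin names the raw post-treatment score, and the section that gives the rule speaks of the "difference in NRS pain score between the treatment group and the control group". On those words the test is reversed. The SD assumptions change the pass rate at D = 0 (0.80 against 0.93) but not the results at +2 and −2. Nor is this a detail left to an analysis plan: the article itself fixes the margin's sign, the confidence limit and the contrast.

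**Conclusion.** The concern holds: the decision rule is wrong as written. With ILM minus TM on the pain score, or on change as week 6 minus baseline, it tests whether ILM is not 2 or more points better and gives no protection against ILM being worse. At the margin of harm the chance of a false claim is about 100% instead of 2.5%; at a true 2-point benefit the chance of success is 2.5%. The conclusion rests on reading the difference in the order written and on the absence of any stated reduction convention. It does not depend on the sample size, the SDs or the rescaling, which affect only the intermediate probabilities. It must be corrected before any comparison by group.

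**What to change.** Choose one outcome and one sign, and use them in the Primary outcome, Sample size calculation and Statistical analysis sections. Either option is enough:

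- **Option A.** Define D as ILM minus TM in NRS change, week 6 minus baseline, so that negative values mean improvement. Declare non-inferiority if the upper limit of the two-sided 95% CI for D is below +2. Replace the margin of -2 with +2 and the lower limit with the upper limit.
- **Option B.** Define the outcome everywhere as pain reduction, baseline minus week 6, with the difference taken as ILM minus TM. Keep the margin of -2 and the lower-limit rule.

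In both cases, replace the post-treatment score in the Sample size section with the chosen outcome, and check that the direction entered in Additional file 2 agrees. The cost is about a sentence in each section and no patients. The article requires Ethics Committee approval for protocol changes, so the amendment should be approved and dated before the analysts see outcomes by group.

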**Materials and methods:**

In the designed Zelen-design randomized controlled non-inferiority clinical trial, a total of 74 patients with KOA will be randomly allocated to one of two interventions: ILM treatment or TM treatment. All participants will receive a 6-week treatment and a follow-up 4 weeks after treatment. The primary outcomes will be the mean change in pain scores on the numeric rating scale (NRS) measured at baseline and the end of last treatment at week 6. The secondary outcomes will be the pain scores on the NRS from weeks 1 to 5 after the start of treatment and the changes from baseline to endpoints (weeks 6 and 10) in the Western Ontario and McMaster Universities Osteoarthritis Index (WOMAC), SF-36, knee circumference, and 6-min walking test. In addition, safety assessment will be performed throughout the trial.

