## Methods

### Study design

The Zelen-design randomized controlled non-inferiority clinical trial will be conducted at Beijing Electric Power Hospital of the State Grid Corporation of China and AMHT Group Aerospace 731 Hospital. The trial protocol is in accordance with the SPIRIT guidelines and the CONSORT guidelines, [26, 27] and the above two checklists are provided as Additional file 1. This trial was approved by the Beijing University of Traditional Chinese Medicine on 17 October 2022 (Ethics Reference No: 2022BZYLL1017). In view of the ethical requirements of current clinical trials, the schedule of recruitment, randomization, informed consent, intervention, and assessment are shown in Fig. 1.

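### The primary NRS comparison is planned without baseline adjustment and on an unsettled variable; a baseline-adjusted ANCOVA gives one arm effect for score or change and usually a tighter interval

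*Protocol article*

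**What the plan says.** The protocol article describes the primary variable in three ways.

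- **Abstract:** the "mean change in pain scores on the numeric rating scale (NRS) measured at baseline and the end of last treatment at week 6". **Primary outcome** agrees: it "is the change in pain from baseline using the NRS index".
- **Sample size calculation:** "The NRS score of the subjects after treatment was taken as the main outcome index".
- **Statistical analysis:** non-inferiority is judged on the "95% confidence interval for the difference in NRS pain score between the treatment group and the control group", without saying whether this is the score or the change. "The margin of non-inferiority is -2", and the lower limit must exceed it.

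The rule for testing is generic to all continuous data. An "independent sample t-test will be used for comparison between the two groups with homogeneity of variance", an unequal-variance t-test is used otherwise, and the "Wilcoxon rank-sum test will be used if data does not conform to a normal distribution". No covariate is named for any outcome. Baseline NRS is measured. Patients come from two hospitals (Study design), and the randomization section states no stratification by hospital.

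**The concern.** In a non-inferiority trial the width of the interval largely decides the result, and this trial is small (37 per arm, planned on 29 evaluable). An unadjusted comparison of week-6 scores ignores what baseline pain predicts. An unadjusted comparison of changes fixes the baseline slope at 1, whatever the data show. The two have different variances, so the power actually available depends on a choice that the article leaves open. A model with baseline NRS as covariate removes that dependence for the treatment estimate and uses data the trial already has.

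**Working it through.** **Inputs from the article (Sample size calculation, Statistical analysis):** margin 2; one-sided alpha 0.025, matching the two-sided 95% CI; power 80%; 29 per group; SDs 26.63 (experimental) and 15.07 (control), which read as 0-100 figures and become 2.663 and 1.507 on the 0-10 scale.

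**Assumed, because the article gives no value:** the correlation r between baseline and week-6 NRS, and the baseline SD b. The true difference is taken as 0.

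**1. The plan's own figure.** With SD s = 2.663 in both arms, the normal approximation gives 2 × 2.663² × (1.960 + 0.842)² / 2² = 27.8, so 28. With the t distribution, SE at 29 per group = 2.663 × √(2/29) = 0.699, non-centrality 2/0.699 = 2.86, power 80.2%; 28 per group gives 78.8%. So 29 is reproduced, for the post-treatment score, after dividing the printed figures by 10 and using the larger SD in both arms.

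**2. SD that drives each analysis**

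- Score t-test: s = 2.663, whatever r is.
- Change t-test: √(s² + b² − 2·r·s·b). At r = 0.3, b = 2.0: √(7.092 + 4 − 3.196) = 2.810. If b = s = 2.663: 2.663 × √1.4 = 3.151.
- ANCOVA on baseline: s × √(1 − r²), giving 2.540, 2.306 and 1.902 at r = 0.3, 0.5 and 0.7. It has 55 rather than 56 degrees of freedom, and the variance is multiplied by 1 + 1/54 for expected chance imbalance.

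**3. A plausible range for b.** Entry requires NRS of 4 or more, so baseline lies in 4-10. The largest possible SD is about 3 (half the patients at 4, half at 10), and an even spread over the integers 4 to 10 gives 2.0. I take 1.2 to 2.0 as the range and show b = 2.663 as the extreme.

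**4. Power at 29 per arm (non-central t)**

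| r | Score t-test | ANCOVA | Change, b = 1.2 | Change, b = 1.5 | Change, b = 2.0 | Change, b = 2.663 |
|---|---|---|---|---|---|---|
| 0 | 80.2% | 79.5% | 73% | 69% | 61% | 51% |
| 0.2 | 80.2% | 81% | 79% | 77% | 71% | 60% |
| 0.3 | 80.2% | 83% | 83% | 81% | 76% | 66% |
| 0.5 | 80.2% | 90% | 90% | 90% | 88% | 80% |
| 0.7 | 80.2% | 97% | 96% | 97% | 98% | 95% |

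The change t-test comes close to ANCOVA where the baseline slope r·s/b is near 1, for example r = 0.5 and b = 1.33. Away from that it loses.

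**5. Width of the 95% CI at 29 per arm.** The half-width is 1.40 for the score t-test. For ANCOVA on baseline it is 1.41, 1.35, 1.23 and 1.01 at r = 0, 0.3, 0.5 and 0.7.

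**6. Same arm effect for score or change.** Week-6 minus baseline, regressed on arm and baseline, differs from week-6 regressed on the same terms only by subtracting 1 from the baseline slope. The arm coefficient is unchanged; a numerical check gave −0.58876 both ways.

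**7. Validity.** In simulation at 29 per arm with r = 0, 0.3, 0.5 and 0.7, all three methods had coverage of about 95%.

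**The case against.** The case against making this a finding has several parts.

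- **The unadjusted t-test is not wrong.** This stands. Under 1:1 randomization, chance baseline imbalance is sampling error that the interval already covers. A reader might infer that the planned test is biased or invalid; neither the article nor the simulation supports that.
- **Covariates are usually left to an analysis plan that is not shown.** This stands only in part. The article does state a method, and that method has no covariate. The conflict over the primary variable is also in the article itself.
- **The plan does not commit to a t-test on change.** Correct. The t-test sentence is generic, the interval is on an unspecified NRS score, and the sample size uses the post-treatment score, for which 29 per arm gives the stated 80% at any r. The change reading comes from the abstract and Primary outcome.
- **The largest power losses need an implausible baseline SD.** This stands. A reader might infer that the trial has only 66% power. That needs r = 0.3, the change variable and a baseline SD as large as 2.663, which the entry rule makes unlikely.
- **2.663 is the larger of the two SDs.** With both, the root mean square is √((2.663² + 1.507²)/2) = 2.164, and the score t-test has about 93% power at 29 per arm, so lost precision would matter less.
- **Adjustment is not free.** Correct, but the cost is small. At r = 0, ANCOVA on baseline has 79.5% against 80.2%, and with hospital added about 78.7%.
- **Hospital.** No stratification is stated, so no gain from adjusting for it can be derived from the document.

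**Conclusion.** The concern holds as a matter of efficiency and clarity, not as an error that invalidates the test. The stated primary comparison has no baseline adjustment and the article does not settle whether it concerns score or change. With week-6 SD 2.663 and 29 per arm, ANCOVA gains about 3, 9 and 17 power points over a score t-test at r = 0.3, 0.5 and 0.7 (83.1, 89.5 and 97.4 against 80.2). Against a change t-test with baseline SD 1.2 to 2.0, it gains between nothing and about 7 points at r = 0.3, and at most about 2 at r = 0.5. On that reading the promised 80% is missed only at low correlation: 76% at r = 0.3 with baseline SD 2.0, and 71-79% at r = 0.2. All of this rests on assumed r and baseline SD.

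A reader might also infer that ANCOVA settles the whole endpoint conflict. It settles the treatment estimate only. The 0-100 inputs set beside a 2-point margin remain. So does the direction of the rule: higher NRS is worse, so a lower limit above −2 for ILM minus TM works only if the variable is a reduction in pain. For the score, or for week 6 minus baseline, the relevant bound is the upper one.

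**What to change.** Before analysis, name one primary variable and make the primary analysis an ANCOVA of week-6 NRS on arm and baseline NRS, with hospital as an optional further term. Define the sign explicitly: for ILM minus TM on the week-6 score, non-inferiority requires the upper limit of the two-sided 95% CI to lie below +2; if the variable is pain reduction, it requires the lower limit to lie above −2. Use the same variable and sign in Primary outcome, Sample size calculation and Statistical analysis.

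No new data are needed. The cost is one degree of freedom (two with hospital), which is under 2 power points against a score t-test when r is near 0. It also needs a protocol amendment: the article requires Ethics Committee approval for changes, and recruitment was already under way. The 0-100 sample-size inputs need a separate correction.
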